# Protocol for disseminating an evidence-based fall prevention program in community senior centers: evaluation of translatability and public health impact via a single group pre-post study

**DOI:** 10.1186/1748-5908-9-63

**Published:** 2014-05-26

**Keywords:** Falls, Community-dwelling older adults, Falls prevention, Tai Ji Quan

## Abstract

**Background:**

Falls are the leading cause of injury death in older adults and present a significant public health problem and a major burden to healthcare. Although there is sufficient evidence from randomized controlled trials to indicate that exercise can prevent falls in older people, few effective, evidence-based fall prevention programs exist in community practice. Thus, there is a pressing need to translate and disseminate evidence-based exercise programs to community providers that serve older adults at increased risk of falling. The current study addresses this public health need by disseminating the evidence-based Tai Ji Quan: Moving for Better Balance (TJQMBB) program through community senior centers.

**Methods/Design:**

The study uses a single-group design in which the TJQMBB program is being delivered to community-dwelling older adults through collaboration with senior centers in selected counties in Oregon, USA, for 48 weeks, followed by a 24-week post-intervention follow-up. Study process and outcome measures will be evaluated in accordance with the components of the RE-AIM framework that focus on Reach, Effectiveness, Adoption, Implementation and Maintenance.

**Discussion:**

This study will determine whether the evidence-based TJQMBB fall prevention program can be disseminated through a broad spectrum of community-based senior centers that often cater to low-income, underserved community-dwelling older adults at risk of falling. If shown to be both practically implementable and sustainable, the TJQMBB program will provide an effective, potentially low-cost, easy-to-implement intervention that could be used by public health practitioners and community-based organizations to address the problem of falls among older adults.

**Trial registration:**

ClinicalTrials.gov Identifier: NCT01854931

## Background

There is little debate about falls in older adults being a significant public health issue [1,2]. It is now well-established that (a) more than one third of community-dwelling adults aged 65 and older fall each year [1], (b) those who fall once are two to three times more likely to fall again [3], (c) most fractures among older adults are caused by falls [4], and (d) falls are the leading cause of injury deaths among individuals over 65 years of age [1,5-7]. All of these facts indicate that falling is a major threat to the independence and quality of life of seniors, in addition to being a significant burden on individuals, society, and national health systems [6,8-10]. From the perspectives of injury prevention and health promotion, this information underscores the need for greater dissemination and implementation of evidence-based fall prevention interventions [11].

Among various exercise programs that focus on increasing lower-extremity muscle strength and improving balance [12,13], Tai Ji Quan exercise has increasingly been demonstrated to reduce the incidence of falls among the elderly [14,15] and people with Parkinson’s disease [16] and is recommended by public health and healthcare experts as an exercise program to improve strength, gait and balance in older adults [3,9]. Thus, testing and translating new evidenced-based Tai Ji Quan programs into community practice to promote well-being and reduce the risk of injuries in older adults has become a public health and injury prevention priority [11,17].

The overarching objective of this study is to disseminate the evidence-based Tai Ji Quan: Moving for Better Balance (TJQMBB) program [18-20] through community senior centers that function to deliver services to America’s older adults [21]. Applying the RE-AIM framework [22], the primary aim of the study is to conduct a process and endpoint evaluation of the TJQMBB program to specifically assess the following relevant public health components (in order of importance):

1. Adoption – to examine the proportion of community senior centers that agree to adopt TJQMBB.

2. Reach – to examine the proportion and representativeness of the older adults who participate in the TJQMBB program.

3. Maintenance – to evaluate, upon completion of TJQMBB, the levels of sustained use of the program within the senior centers delivering the TJQMBB program and sustained participation in Tai Ji Quan exercises by participating individual older adults.

4. Implementation – to determine the degree to which the various TJQMBB program elements are delivered as intended.

5. Effectiveness – to examine the degree to which fall incidence is reduced and physical performance measures are improved.

A secondary aim of the study is to conduct a preliminary cost-effectiveness analysis of the TJQMBB program.

## Methods

### Study design overview

Within the RE-AIM framework [22], which is widely used for evaluating the public health impact of health promotion interventions and healthcare programs, we will evaluate the effect of our TJQMBB program via a 48-week, single-group, pre-and-post design with a 24-week post-intervention follow-up. The pre-and-post design allows us to assess the components of Adoption, Reach, Implementation and Effectiveness during the active 48 weeks of the intervention, whereas the 24-week post-intervention follow-up is planned to assess short-term program Maintenance.

### Study area

The dissemination area for this project is four counties in the state of Oregon, USA: Clackamas, Lane, Multnomah and Washington. The total population of these counties in 2012 was 2,045,327, of which 259,747 were persons 65 years old and over (per U.S. Census estimates), which accounted for 45% of the older adult population in the state. Per CDC data, these four counties ranked highest in Oregon in terms of the number of unintentional falls between 2004 and 2010 in individuals aged 65 and older, with the average annual (unintentional) fall fatality crude rate (per 100,000) being 85.8 in Clackamas, 73.2 in Lane, 89.9 in Multnomah, and 74.9 in Washington, compared with the national rate of 47.8 per 100,000 [23]. Within these counties, local community senior centers (defined below) constitute the primary locations where the TJQMBB program is disseminated and implemented.

### Dissemination adopters and population

In line with our pilot work [18], the program disseminating partners are community senior centers that provide health resources and social services, including meals and physical or recreational activities as part of a comprehensive service program to local community-living older adults. According to a list compiled from combined sources (*i.e*., local Area Agencies on Aging, county and state Senior & Disability Services, Oregon Recreation & Park Association), approximately 50 senior centers within the study area were potential candidates for our study.

Community-dwelling adults aged 65 and over living within the defined study area are the target population because this age cohort (a) is most at risk of falling [2,6,24] and (b) has been the target population for fall prevention in previous studies [12,13]. Participants are eligible to be enrolled in the TJQBMM program if they are (a) physically mobile (*i.e*., can walk with or without an assistive device), (b) without severe mental deficits, as determined by Mini-Mental State Evaluation (≥ 19) [25], (c) able to obtain a medical provider’s clearance, and (d) able to commit to the 48-week duration of the study.

### Recruitment

#### Senior centers

Eligible senior centers are initially contacted by research staff to solicit or confirm their interest in participating in this dissemination project. At the point of contact, a full description of the TJQMBB program is discussed with the center manager, program coordinator, or supervisor. When a center expresses interest in participating, a logistical plan that covers program/class promotion and set-up, size of the class, recruitment of participants, and class start-up date and scheduling is made jointly between the project staff and the participating center.

On the basis of available classroom sizes at the center, a maximum number of class enrollments is determined in consultation with staff at the participating center. The TJQMBB program advertisement and promotion is primarily done in collaboration with the participating center using sources such as monthly or quarterly newsletters, center websites, in-house flyers and class sign-up sheets, and word of mouth.

#### Participants

Prospective participants who respond to the promotion and/or sign up for the class at each center are contacted by telephone by the research staff to initiate a phone screening for initial eligibility. This is followed by an in-office visit where a full description of the program is given, consent forms are obtained, and study baseline measures are collected.

#### TJQMBB intervention

The TJQMBB program implemented was developed on the basis of early trials [14,26], modified in a community-based pilot project [18], and further refined and updated in two additional studies [16,19]. The full background of the evolution of this program is described elsewhere [20].

Per program protocol, each session begins with warm-up exercises (5 to 10 minutes) based on Tai Ji Quan movements, followed by the teaching and practice of core movements and subroutines that involve single forms and mini therapeutic movements (40 to 45 minutes), and ending with a simple set of breathing exercises (3 to 5 minutes). The core training protocol, which involves a set of simple but functional Tai Ji Quan-based actions, focuses on stimulating and integrating musculoskeletal and sensory systems via self-initiated movements such as weight shifting from foot to foot, unilateral weight-bearing, trunk rotation/flexion, ankle sways, and coordinated eye-head-hand movements, executed with integrated cognitive tasks [27]. The goal of the training is to improve postural stability and orientation, limits of stability, gait initiation and locomotion, gaze stability, movement symmetry and coordination, and lower-extremity strength. Chair-supported progressions, from completely seated, through sit-and-stand, to chair-assisted, are also included to: (a) meet the specific needs and performance capabilities of participants; and (b) train for functional activities involved in daily living.

A copy of a DVD with selected forms/movements of the program is distributed to all participants 4 to 6 weeks into the program. Participants are encouraged to use the material for additional home practice.

#### Class instructors

All instructors are chosen from local communities. In an effort to make the program more easily disseminable and generalizable, special efforts are made to recruit individuals who have little or no background in Tai Ji Quan or who currently work at participating centers giving instruction in other exercise modalities.

The first author trains all instructors via a two-day workshop at the Oregon Research Institute, using the training materials already developed. The training protocol includes a discussion of the theoretical underpinnings that were used to develop the program, findings from the efficacy trials and dissemination studies, detailed information and hands-on drills with the forms, variations of forms and routine exercises, mini therapeutic movements, and discussion of implementation- and teaching-related issues. Instructor training emphasizes consistency of delivery to ensure generalizability across different implementation centers. After instructors begin teaching, brief refresher training sessions are provided on a monthly basis.

### Measures

#### Demographics

General information that describes the social demographics of participating centers and their older adult clients is collected at baseline. Information on participating centers includes: types and number of services provided (*e.g*., meal services, education, physical activity); number of rooms devoted to physical activity; average class attendance across programs offered; and number of full- and part-time staff. Information on participants includes demographic and health characteristics, including age, gender, marital status, living situation, education, family income, race/ethnicity, existing medical conditions, use of medication, body weight, and body height. In addition, information regarding types of services received and frequency of visits to the service providers is also collected.

#### RE-AIM measures

Each component is operationalized per our study aim and assessed per procedures outlined by the RE-AIM developers (http://www.re-aim.org/) as described below.

Adoption is defined as the absolute number, proportion and representativeness of the senior centers that agree to adopt the TJQMBB program. Accordingly, we will calculate the adoption rate by dividing the number of centers that agree to participate (numerator) by the total number of centers approached within the dissemination geographic area (denominator). We document and report in detail on the following components: (a) total number of centers approached within the study area, (b) total number of centers that express interest in participating, (c) total number of centers that decline to participate (and reasons for declining), (d) total number of centers not responding to program promotion, (e) total number of centers participating, and (f) characteristics of participating centers. As part of the evaluation, the representativeness of participating centers will be determined by comparing them with the overall service characteristics of all senior centers in Oregon.

Reach is defined as the absolute number, proportion and representativeness of the older adults who participate in the TJQMBB program. This indicator will be assessed by first calculating the participation rate, using the number of eligible people qualified per study criteria and enrolled (numerator) divided by the total number of older adults who respond to the program promotion (denominator). In addition, we will also evaluate Reach by using the total number of older adults who attend regular activities at the participating centers as a denominator, which gives us a population index on the Reach component. In assessing the representativeness of our study population, we will compare information on demographics and health status of those who participated with those who met our recruitment criteria but who eventually, for any reason, declined to participate.

Maintenance is defined as the level of continued adoption of the TJQMBB program at the participating senior centers and sustained participation in Tai Ji Quan practice among the study participants after the completion of the 48-week active class implementation. At the center level, we will determine the number of participating centers that either continue offering the class or plan to adopt it in the future. At the individual participant level, we continue to collect data during the 24-week post-intervention follow-up with regard to participant Tai Ji Quan exercise status (*i.e*., continuing vs. not continuing) and with respect to time (length of practice sessions) and frequency (number of sessions per week).

Implementation is defined as the degree to which instructors deliver the various intervention elements as intended. In this regard, measures of fidelity from our previous studies of this program are used [16,19]. Specifically, the extent to which the program is implemented per the pre-specified requirements is assessed in relation to the extent to which class instructors successfully implemented the various program components, including (a) delivering twice-weekly 60-minute sessions over a 48-week period (verified by project staff), (b) adhering to the teaching emphases and training protocols (verified by a checklist), and (c) achieving participation and retention rates of 70% or better (verified by class attendance sheet). The components in adherence to the teaching and training protocols focus primarily on delivery (*i.e*., teaching emphases and movement execution), integration (*i.e*., blending of forms, variations of forms, and mini therapeutic movements), and actual practice time (40 to 45 minutes spent on core movements). The first author or an experienced peer instructor conducts in-class fidelity checks at least every two months.

As part of the evaluation for our secondary study aim, the implementation component will include documenting project implementation costs. Specifically, direct costs associated with implementation of the intervention will be documented, including (a) participant recruitment costs (administration staff costs, printed materials for program promotion, advertisements), (b) instructor liability insurance costs, (c) instructor salary costs, (d) classroom rental costs in the local community, (e) cost of the initial two-day training and refresher courses for instructors, as well as in-class fidelity checks, and (f) other expenses related to program promotion and supplies (*e.g*., water bottles, DVDs).

Effectiveness in this study is defined as the degree to which fall incidence is reduced and physical performance measures have improved. Specifically, falls are assessed using fall counts, recorded by each participant in a daily ‘fall calendar’. Participants are instructed to record any fall event and to indicate whether the fall caused them to seek medical attention. A fall is defined as ‘when you land on the floor or the ground, or fall and hit objects like stairs or pieces of furniture, by accident’. A fall is considered ‘injurious’ if the fall resulted in fractures, head injuries, sprains, bruises, scrapes, or other serious joint injuries, or if the individual sought medical care. As in our previous studies [14,16,19], falls are monitored for all participants throughout the 48-week intervention, or until the date they withdrew from the study.

In addition, physical performance-based measures are collected. These include (a) Timed Up & Go test [28], (b) Multi-Directional Reach Test (in three directions – forward, backward, lateral) [29], (c) chair stands [30], and (d) 50-foot speed walk.

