### Innovation

To our knowledge, this is the first Tai Ji Quan study to adopt a community-based approach to evaluate an evidence-based program that has already undergone research trials and initial adaptations in local community settings. Such a study is sorely needed given the consequences of falling for older adults, the accumulated evidence of Tai Ji Quan efficacy in reducing risk of falling, and the need for translating evidence-based research into community-based programs that are accessible through local senior and adult activity centers. Second, the effort to evaluate the success of the program via the well-established RE-AIM framework is also novel, providing a theoretically sound approach for evaluating the program’s potential for translation from research to community practice. Finally, the emphasis on training existing instructors and/or staff in the implementation centers is also a novel approach in that it will both facilitate class teaching and program sustainability and potentially reduce program costs. Also, it is well documented that sustaining important public or grant-funded services after initial funding is terminated is a major public health challenge. Our study responds to this challenge in that it involves significant collaboration with community adopters, allowing us to formally evaluate the sustainability of the program over time at the service provider level.

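### Centre-level Maintenance is defined as continued adoption but counted to include centres that only plan to offer the class later, so the count can overstate sustained use

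*Protocol article*

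**What the plan says.** The protocol article lists five RE-AIM components in order of importance, and Maintenance is third. The centre-level part of that aim (Background) is to evaluate "the levels of sustained use of the program within the senior centers delivering the TJQMBB program". Under RE-AIM measures, Maintenance is defined for centres as "the level of continued adoption of the TJQMBB program at the participating senior centers", assessed "after the completion of the 48-week active class implementation". The Study design overview ties this to a time window: "the 24-week post-intervention follow-up is planned to assess short-term program Maintenance".

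The operational rule for centres, also under RE-AIM measures, is: "we will determine the number of participating centers that either continue offering the class or plan to adopt it in the future". The participant-level rule that follows it records actual exercise status ("continuing vs. not continuing") with session length and weekly frequency, collected during the 24-week follow-up.

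The Innovation section says that collaboration with community adopters is a strength of the study, "allowing us to formally evaluate the sustainability of the program over time at the service provider level".

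**The concern.** The definition and the measure describe different things. Continued adoption and sustained use are facts about what a centre is doing. A plan is a statement about what it may do. The rule joins the two with an either/or condition and yields one number.

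The second condition can add only centres that are not currently offering the class, because those that are offering it already meet the first. Every centre it adds is therefore one that, at the time of assessment, is not continuing.

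At stake is how the sustainability result can be read. Maintenance ranks above Implementation and Effectiveness, and the article presents evaluation at the service-provider level as an answer to the problem of services lapsing once initial funding ends. A pooled count does not show how many centres kept the programme running.

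**Working it through.** The document states no Maintenance figure, so there is nothing to reproduce. The check has two parts.

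**1. Comparing the texts**

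| Place in the protocol article | What counts as Maintenance |
|---|---|
| Background, aims | Sustained use within delivering centres |
| RE-AIM measures, definition | Continued adoption after the 48 weeks |
| RE-AIM measures, centre-level rule | Still offering, or planning to |
| RE-AIM measures, participant-level rule | Actual status: continuing or not |

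Only the centre-level rule admits intention. The definition, the aim and the participant-level rule all refer to actual use.

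**2. Size of the discrepancy**

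Let N be the number of participating centres, C the number still offering the class, and P the number not offering it but stating a plan.

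- Continued adoption as defined: C
- Count under the stated rule: C + P
- Overstatement: (C + P) − C = P, where 0 ≤ P ≤ N − C

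N is not given. The only related figure is the pool of candidates: "approximately 50 senior centers within the study area were potential candidates for our study". That is an upper bound on N, not an estimate of it.

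As shares, let c = C/N and let p be the proportion of the non-delivering centres that state a plan. Then:

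- Reported share = c + (1 − c)p
- Overstatement = (1 − c)p

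The article gives neither c nor p. The values below are assumptions, chosen only to show the scale.

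| c (assumed) | p (assumed) | Overstatement (1 − c)p | Reported share |
|---|---|---|---|
| 0.40 | 0.25 | 0.60 × 0.25 = 0.15 | 0.55 |
| 0.40 | 0.50 | 0.60 × 0.50 = 0.30 | 0.70 |
| 0.60 | 0.25 | 0.40 × 0.25 = 0.10 | 0.70 |
| 0.60 | 0.50 | 0.40 × 0.50 = 0.20 | 0.80 |

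The overstatement rises with p and falls with c, so over these ranges its limits are the corner values: 10 points (c = 0.60, p = 0.25) and 30 points (c = 0.40, p = 0.50).

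The second and third rows both report 70%, although actual delivery is 40% in one and 60% in the other. The pooled figure alone cannot tell these situations apart.

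**The case against.** The strongest reply is that this is a descriptive count in a condensed article. The sentence could be followed while listing the two groups separately, and tabulation is often left to the full protocol or analysis plan. It is true that separate reporting would be compatible with the text. However, the article does not commit to it, and the point concerns a rule that is stated, not a detail that is omitted. As written, the rule gives one number for either condition, under a construct defined as continuation.

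The article also says that components are assessed by the RE-AIM developers' procedures, which might accept planned continuation. That cannot be checked from the document. It would not remove the mismatch with the article's own definition and aim.

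Several stronger readings are tempting but not supported:

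- **That a stopped centre passes as a success.** The article sets no threshold or pass/fail rule for Maintenance, so no decision changes. A stopped centre with no stated plan is not counted.
- **That the measure has no denominator.** The rule concerns participating centres, and the total participating is among the items to be reported under Adoption, so a reader can form the proportion.
- **That no time frame exists.** Maintenance is placed after week 48, and the 24-week follow-up is assigned to it. Only an exact date for the centre-level assessment is absent.
- **That centres will overstate their plans to please the study team.** This is plausible, but the document says nothing about it, and the point does not depend on it. Even sincere plans are not continued adoption.

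**Conclusion.** The concern holds in a limited form. The stated centre-level count is wider than the construct it is meant to measure, and it overstates continued adoption by exactly the number of planning-only centres. The direction is certain: the error is zero or positive. Its size is unknown. The 10 to 30 percentage points rest wholly on the assumed 40-60% delivering and 25-50% of the remainder planning, and the overstatement would be zero if no stopped centre stated a plan. The consequence is an inflated and hard-to-interpret descriptive figure on a component ranked third in the primary aim, not a changed test result or trial decision. It should be corrected because the correction is small and the article relies on this measure for its claim about sustainability.

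**What to change.** Define centre-level Maintenance as the number of participating centres actually offering the class at the end of the 24-week post-intervention follow-up, divided by all participating centres. Report centres that are not offering it but plan to do so on a separate descriptive line, outside the numerator.

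The cost is mainly wording plus an assessment date. The article describes data collection during the 24 weeks only for individual participants, so a brief status check with each centre at that point may have to be added if it is not already planned. The reported Maintenance figure may be lower than under the present rule.
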